### 4.4. Data Analysis

A descriptive analysis by groups (intervention and control) of participants’ sociodemographic, functional, and clinical characteristics will be carried out to identify potential differences between the two study groups, with quantitative variables expressed as either means and standard deviations or medians and interquartile ranges depending on the normality or skewness of data distribution. Qualitative variables will be summarized as frequencies and percentages. Data on the effect of the health education intervention will be analyzed in both the intention-to-treat population and the per-protocol population. In the former case, all participants will be included and will be analyzed as part of the group to which their PCF will be randomly assigned. Should the percentage of missing data be higher than 5%, multiple imputation techniques will be used. In the per-protocol analysis, complete cases of patients will be included provided they have maintained adherence. The intervention group is required to be adherent and have at least 80% attendance at the initial five sessions. Safety, acceptability, and feasibility of the health education intervention will also be assessed.

The primary efficacy analysis, (FOF), will be the comparison between intervention and control groups fitting a fixed-effects ANOVA model. Model will include group and facility as independent variables, with facility being a nested factor within group. The short FES-I scale mean scores and their 95% confidence intervals will be provided for each facility, or by groups if no differences between facilities are observed. The effectiveness of the health education intervention in relation to fear of falling will be measured through the decrease in the short FES-I scale scores, assessed at three times: at 1-, 6- and 12 months after the intervention. The difference in means between the intervention and control groups will be analyzed. In addition, the variable will be examined dichotomously, using a cut-off point on the short FES-I scale of 11 or more to identify the presence of fear of falling. Multivariate models will be fitted to identify factors potentially related to FOF.

For the secondary outcome variable (incidence of falls), a process similar to the main analysis will be followed, but this time fitting a fixed-effects logistic regression model, again nesting each facility within its group. The effectiveness of the health education intervention for the incidence of falls will be measured through the recording of falls (recorded in the medical history or reported by the patient), at 1-, 6- and 12-months post intervention. Both groups will be compared in terms of odds ratios, and their corresponding 95% confidence intervals will be provided.

To assess the impact of the health education intervention by time, mixed effects models will be adjusted, including time also as an independent variable and random intercepts for participants.

Data will be recorded in a paper data collection notebook and entered into an Excel spreadsheet by a single researcher in order to minimize the risk of transcription errors. The collected data will then undergo a second review to correct transcription errors, if necessary. Access to these data will be limited to authors until open access dissemination, after which they can be included on ClinicalTrials.gov.

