### 2.7. Sample Size

We expect to be able to recruit ten PCFs (five assigned to the intervention group and five to the control group). Assuming a significance level of 0.05, a difference of 3.8 points on the Short Falls Efficacy Scale-International (FES-I), a standard deviation of 5.1 points, and an intraclass correlation coefficient of 0.1, at least 12 participants will be required per center (a total of 120 participants) to reach a power of 80%. Allowing for a loss of 20%, the necessary sample size will be 150 individuals (75 patients assigned to the intervention group and 75 to the control group; approximately 15 patients in each PCF, about five patients per nurse).

Patients seen by nurses at each participating facility and meeting the eligibility criteria will be recruited using a consecutive sampling method until the required sample size—which will be the same for all participating facilities—has been reached.

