### 2.8. Randomization

Ten PCFs will be randomly assigned to the intervention or control group, resulting in five facilities per arm. An allocation ratio of 1:1 will be used. The randomization will be performed using a random number generator. The study coordinator will run the generator and place the allocations into sealed envelopes.

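### The primary ANOVA treats the randomised facilities as fixed effects, so the group test omits between-facility variance; at the planned ICC of 0.1 a 5% two-sided test runs at about 20%

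*Protocol article*

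**What the plan says.** - **Unit of randomisation (Protocol article, 2.8 Randomization):** "Ten PCFs will be randomly assigned to the intervention or control group, resulting in five facilities per arm".
- **Sample size (2.7):** the inputs are a 5% significance level, a 3.8-point difference on the short FES-I and a standard deviation of 5.1. The clustering allowance is "an intraclass correlation coefficient of 0.1, at least 12 participants will be required per center", which gives 120 evaluable participants for 80% power and 150 recruited after 20% loss.
- **Primary analysis (4.4 Data Analysis):** the arms are compared by "fitting a fixed-effects ANOVA model. Model will include group and facility as independent variables, with facility being a nested factor within group".
- **Display of results (4.4):** mean scores with 95% confidence intervals are to be given "for each facility, or by groups if no differences between facilities are observed". The same paragraph also says, without any condition, that the difference in means between the arms will be analysed.
- **Falls (4.4):** a fixed-effects logistic regression, with facility again nested in group.
- **Effect over time (4.4):** "mixed effects models will be adjusted, including time also as an independent variable and random intercepts for participants".

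Facility is nowhere a random effect. No cluster-level test and no cluster-robust standard error is named.

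**The concern.** The facility is what was randomised, so the chance difference between arms includes differences between facilities. A valid test of the intervention has to measure its effect against that variation, for which five facilities per arm leave 8 degrees of freedom. A nested ANOVA with every effect fixed uses the within-facility mean square instead, with 110 to 140 degrees of freedom. Nesting removes facility differences from the residual but does not put them into the error of the group contrast.

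The sample size section budgets for between-facility variance, and the analysis section then leaves it out. At stake are the error rate and the confidence interval of the confirmatory result on the primary outcome. Section 6 would use that result to recommend integration into routine primary care, which is a claim beyond these ten facilities.

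**Working it through.** **Inputs.** From 2.7: difference 3.8, SD 5.1, ICC 0.1, 12 evaluable or 15 recruited per facility, alpha 0.05. From 2.8: five facilities per arm. Sidedness is not stated; two-sided is assumed because it reproduces the stated sample size.

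**1. The plan's own figure.** Individually randomised n per arm = 2·(5.1·(1.96 + 0.84)/3.8)² ≈ 28.3, or 29 rounded up. Design effect = 1 + (12 − 1)·0.1 = 2.1. Required per arm = 59.4 (unrounded) to 60.9 (from 29), against 5 × 12 = 60. Normal-approximation power at 60 per arm is 80.4%, and 120/0.8 = 150. The sample size reproduces, and it does so only with between-facility variance counted.

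**2. What the fixed-effects test uses.** Let m be participants per facility, ρ the ICC, and total variance 5.1². With no intervention effect, the expected group mean square is the within-facility variance plus m times the between-facility variance. The denominator has only the within-facility part. The ratio is

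R = 1 + m·ρ/(1 − ρ).

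The true two-sided type I error is 2·P(t > t₀.₉₇₅/√R) on 10m − 10 degrees of freedom.

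- m = 12: R = 1 + 12·0.1/0.9 = 2.33; 1.982/1.528 = 1.297 on 110 df; error 19.7%.
- m = 15: R = 1 + 15·0.1/0.9 = 2.67; 1.977/1.633 = 1.211 on 140 df; error 22.8%.

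A simulation of 200,000 null trials per facility size gave 19.7% and 22.8%. The test on facility means with 8 df gave 5.0% in both cases.

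**3. Direction.** Half of these rejections favour control. False benefit is therefore 9.9% (m = 12) or 11.4% (m = 15), against 2.5%.

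**4. Sensitivity to the ICC.**

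| ICC | m = 12 | m = 15 |
|---|---|---|
| 0.01 | 6.4% | 6.8% |
| 0.02 | 7.8% | 8.6% |
| 0.05 | 12.4% | 14.2% |
| 0.10 | 19.7% | 22.8% |
| 0.15 | 26.4% | 30.2% |

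**5. Confidence interval, m = 12.**
- Fixed-effects SE = √(0.9·5.1²·2/60) = 0.88; half-width 1.982·0.883 = 1.75.
- True SE = 5.1·√(2·2.1/60) = 1.35; half-width on 8 df 2.306·1.349 = 3.11.

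**6. By-time mixed model.** Assume a within-person correlation of 0.6, three follow-up visits and total variance 1, split as facility 0.1, person 0.5 and residual 0.4. A person's mean over visits then has variance 0.5 + 0.4/3 = 0.633 within facility and 0.1 between facilities, an ICC of 0.1/0.733 = 0.136. With participant intercepts only, the design effect ignored for the time-averaged group effect is 1 + 11·0.136 = 2.5 (m = 12) or 1 + 14·0.136 = 2.91 (m = 15). Then 2·P(Z > 1.96/√2.5) = 21.5% and 2·P(Z > 1.96/√2.91) = 25.0%; simulation gives about 22% and 26%. For a group-by-time contrast, a facility effect that is constant over time cancels within each person, and simulation gives 4.7 to 5.1%.

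**7. Power of the valid test on 8 df.**
- m = 12: 3.8/1.349 = 2.82; power about 69%.
- m = 15: SE = 5.1·√(2·2.4/75) = 1.29; 3.8/1.29 = 2.95; power about 73%.

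**The case against.** **Fixed facilities are legitimate for a conclusion about these ten facilities.** That is true, but it is not the conclusion planned. The protocol assumes an ICC, justifies clustering by implementation at organisational level (4.5) and foresees wide adoption (Section 6).

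**The 20% depends on the ICC.** This stands. Effectiveness is to be judged on the decrease in score, and 2.7 does not say whether 0.1 refers to scores or to change. Stable facility differences largely cancel in change, so a smaller ICC is plausible. The error still exceeds 5% at every positive ICC.

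**Stronger readings that the text does not support:**
- A reader might infer that a useless intervention has a 1 in 5 chance of being declared beneficial. The 20% counts both directions; false benefit is about 1 in 10.
- A reader might infer that no group estimate is given once facilities differ. The conditional sentence governs which mean scores are shown. The between-group difference is promised without condition, and so are the odds ratios for falls.
- A reader might put a frequency on that condition. A 5% F test for facilities would be significant in about 55% (m = 12) to 65% (m = 15) of trials at ICC 0.1, but the protocol names no test or threshold.
- A reader might extend the fault to everything from the by-time models. The text does not say which effect is tested, and a group-by-time contrast is unaffected if facility effects are constant over time.

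**A later analysis plan could settle this.** An omission could be left to it. Here the article positively specifies fixed effects for both outcomes, and a plan that followed it would carry the error forward.

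**Conclusion.** The concern holds for the error term of the primary analysis and should be corrected before the data are analysed. At the protocol's own ICC of 0.1 the fixed-effects group test has a two-sided type I error of about 20% (12 per facility) to 23% (15), and its interval is a little over half the width it should be. These figures assume equal facility sizes, normal errors, a two-sided test and inference beyond the ten facilities; at ICC 0.02 the inflation is modest. The logistic model for falls shares the structure, though no error rate was computed for it. The by-time model shares the fault for a time-averaged group effect only.

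**What to change.** - **Primary analysis:** replace the ANOVA with a linear mixed model that has group fixed, a facility random intercept and Kenward-Roger or Satterthwaite degrees of freedom. A t-test on facility means with 8 df is an equivalent choice.
- **Falls:** treat facility as random in the logistic model, or use a cluster-level analysis.
- **By-time models:** add a facility random intercept to the participant intercepts, and state which group effect is tested.
- **Reporting:** always give the group difference with its confidence interval. Present facility means as descriptive, and drop the condition on observed facility differences.

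**Cost.** Only analysis wording changes; recruitment, visits and data collection stay as they are. The confidence interval becomes wider. Power for 3.8 points on 8 df is about 69% with 12 per facility and 73% with 15, so the 80% in 2.7 should be restated, and the sponsor should accept that shortfall knowingly.

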#### 2.11.1. Primary Outcome Variable

The seven-item short FES-I scale (Spanish adaptation) scores will be collected at baseline, one month, six months, and one year after the health education intervention. The scale is validated for use with Spanish speakers, with a range of 7–28. A score equal to or greater than 11 is considered positive for FOF (see Table 1). The short FES-I scale showed a Cronbach’s alpha of 0.88 compared to the long version. In addition, the short FES-I obtained a Spearman’s rho correlation coefficient of 0.99 between T1 (measurement at baseline) and T2 (measurement at one month), as well as an intraclass correlation coefficient of 0.77 between T1 and T2 [32].

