## Figures and Tables

**Figure 1 healthcare-12-02510-f001:**
[figure not shown]
CONSORT flowchart of participants.

**Table 1 healthcare-12-02510-t001:** Short FES-I scale.

Short FES-I Scale How Concerned Are You About the Possibility of Falling While…?	Not at All Concerned	Somewhat Concerned	Fairly Concerned	Very Concerned
1. Getting dressed or undressed	1 □	2 □	3 □	4 □
2. Taking a bath or shower	1 □	2 □	3 □	4 □
3. Getting in or out of a chair	1 □	2 □	3 □	4 □
4. Going up or down stairs	1 □	2 □	3 □	4 □
5. Reaching for something above your head or on the ground	1 □	2 □	3 □	4 □
6. Walking up or down a slope	1 □	2 □	3 □	4 □
7. Going out to a social event (e.g., religious service, family gathering or club meeting)	1 □	2 □	3 □	4 □
SUBTOTAL:	Add all the 1’s	Add all the 2’s	Add all the 3’s	Add all the 4’s
	Short FES-I ≥ 11: Fear of falling			

**Table 2 healthcare-12-02510-t002:** Summary of visits and variables.

Variables	Visits						
	Initial Visit. Screening	Pre-Intervention Baseline visit ^1^	Five Initial Group Sessions	Visit Post Initial Intervention ^2^	Visit at Six Months Post Initial Intervention ^3^	Booster Session	Visit at 12 Months ^4^
Review of eligibility criteria	x						
Informed consent	x	x					
Primary outcome variable: Short FES-I		x		x	x		x
Secondary outcome variable: Post intervention falls		x		x	x		x
EXPLANATORY VARIABLES							
Sociodemographic variables		x					
Functional variables		x			x		
Usual footwear		x			x		
Clinical variables		x					
Falls during intervention				x		x	
Ability to practice self-care		x		x	x		x
Perceived health and anxiety		x		x	x		x
Acceptability (among patients)				x			

^1^ ±2 weeks before the health education intervention (for the intervention group: (IG)). ^2^ ±2 weeks after the initial sessions (IG). ±4–8 weeks after randomization (for the control group (CG)). ^3^ ±2–4 weeks, at six months after randomization (CG) or after the initial health education intervention (IG), always prior to the booster session. ^4^ ±2–4 weeks, at 12 months post randomization (CG), at six months after the booster session (IG).

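### The primary FES-I model leaves its response unclear (score or decrease) and, on either reading, does not use baseline FES-I as a covariate

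*Protocol article*

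**What the plan says.** Section 4.4 (Data Analysis) says that the primary efficacy analysis "will be the comparison between intervention and control groups fitting a fixed-effects ANOVA model". It then gives the terms: "Model will include group and facility as independent variables", the facilities being nested in their arm. No baseline covariate is listed.

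The same paragraph describes the effect in two ways. Effectiveness "will be measured through the decrease in the short FES-I scale scores, assessed at three times", namely 1, 6 and 12 months, which reads as change from baseline. It also promises mean scores with confidence intervals, and states: "The difference in means between the intervention and control groups will be analyzed". Whether these are means of scores or of changes is not said.

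Baseline FES-I is available for everyone. Section 2.11.1 says that the "scores will be collected at baseline, one month, six months, and one year after the health education intervention", Table 2 marks the baseline visit in the row "Primary outcome variable: Short FES-I", and section 2.6.1 requires a score of at least 11 for entry.

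No other planned model fills the gap. The multivariate models in section 4.4 look for factors related to fear of falling. The mixed models in the same section add time and participant intercepts to describe the effect over time. Neither is the primary comparison.

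**The concern.** The baseline value of an outcome is usually the strongest predictor of its later value, and here it costs nothing because it is already collected. The article names the model and its terms, so leaving baseline out is a stated choice and not a detail deferred to an analysis plan.

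Two things are at stake. The first is precision. The analysis of the follow-up score ignores baseline. The analysis of change uses it with a slope fixed at 1, which adds noise when the correlation is low.

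The second is chance imbalance. Section 2.8 randomises ten facilities with a random number generator and describes no stratification or restriction. The balancing measures in section 4.5 concern group size, attrition, eligibility and training, not baseline FES-I. Section 4.4 plans a descriptive look at group differences, but the primary model makes no use of what it shows.

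**Working it through.** **Inputs from the protocol article.** Section 2.7: difference 3.8, SD 5.1, ICC 0.1, alpha 0.05, power 80%, 12 participants per facility, five facilities per arm, 20% loss. Section 2.11.1: one-month test-retest ICC 0.77.

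**Assumptions.** Alpha is two-sided. The 5.1 is the SD of the follow-up score. The correlation r between baseline and follow-up is the same at participant and facility level. The documents give no r for 6 or 12 months, so I use 0.3 to 0.77. The baseline SD is not given, so I use 4 to 5.1.

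**1. The plan's own figure.** Per arm without clustering: 2 × [5.1 × (1.960 + 0.842) / 3.8]² = 28.3. Design effect: 1 + 11 × 0.1 = 2.1. Product: 59.4, so 60 per arm = 5 × 12, or 120 in all; 120 / 0.8 = 150. The stated sizes reproduce. The standard error of the arm difference is 5.1 × √(2 × 2.1 / 60) = 1.35. Power is Φ(3.8 / 1.349 − 1.960) = 80.4%.

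**2. Power by response and model.** Variance relative to the follow-up score alone is 2(1 − r) for a change score with equal SDs, and 1 − r² with baseline as covariate. Each is applied to the standard error of 1.349, with the same normal approximation.

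| r | Follow-up score | Change score: SE, power | Baseline-adjusted: SE, power |
|---|---|---|---|
| 0.3 | 1.35, 80.4% | 1.60, 66.3% | 1.29, 83.9% |
| 0.5 | 1.35, 80.4% | 1.35, 80.4% | 1.17, 90.2% |
| 0.77 | 1.35, 80.4% | 0.92, 98.6% | 0.86, 99.3% |

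A simulation of 5 + 5 facilities of 12 agreed with these standard errors (for example 1.59 and 1.28 at r = 0.3).

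**3. The same with a smaller baseline SD.** With baseline SD 4 and follow-up SD 5.1 the ratio is 4 / 5.1 = 0.784. The change-score factor is 1 + 0.784² − 2r × 0.784 = 1.144, 0.831 and 0.407 at r = 0.3, 0.5 and 0.77. Power is then 74.9%, 87.1% and 99.3%. The adjusted analysis stays at 83.9%, 90.2% and 99.3%. A change score now beats the raw score once r exceeds 0.784 / 2 = 0.39, not 0.5.

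**4. Chance baseline imbalance.** The standard error is SD × √(2 × design effect / number per arm). A third of the target is 3.8 / 3 = 1.27 points.

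| Baseline SD | Per facility | SE | P(absolute imbalance ≥ 1.27) |
|---|---|---|---|
| 5.1 | 12 | 1.35 | 35% |
| 5.1 | 15 | 1.29 | 33% |
| 4 | 12 | 1.06 | 23% |
| 4 | 15 | 1.01 | 21% |

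**5. What a one-SE imbalance does.** With equal SDs and 12 per facility, a baseline difference of 1.35 shifts the raw-score comparison by r × 1.35 = 0.40, 0.67 and 1.04 points at r = 0.3, 0.5 and 0.77. It shifts the change-score comparison by (r − 1) × 1.35 = −0.94, −0.67 and −0.31 points. Baseline adjustment removes the shift in expectation.

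**The case against.** Several objections have force.

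- **Baseline may already be used.** A decrease is naturally measured from baseline. A reader might infer from the two model terms that imbalance goes wholly uncorrected, but the decrease wording does not support that. If change is the response, imbalance is over-corrected. What stands is that the response is unclear and that neither reading uses baseline with an estimated slope.
- **The gain may be small.** Entry at 11 or more confines baseline scores to 11 to 28. Even a uniform spread over that range has an SD of about 5.2, so a baseline SD of 5.1 is probably high. With SD 4 the advantage over a change score shrinks (step 3), and at r = 0.77 it nearly disappears on either SD. This limits the size of the point but does not reverse it, because adjustment is never worse in the cases examined. The 0.77 is a one-month test-retest figure; correlation at 6 or 12 months in people selected on a high score may be lower.
- **The 5.1 may be the SD of a change.** Section 2.7 does not say. If it is, an unadjusted change analysis has the planned precision and the change-score column above does not apply.
- **A raw comparison of randomised arms is unbiased over randomisations.** True. The bias here is conditional on the imbalance that this one trial happens to draw.

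A reader might also infer that adjustment is needed to recover power lost to a test on 8 degrees of freedom. The stated model is a fixed-effects ANOVA, and the stated power follows the normal approximation. How facility enters the error term is a separate question, and this point does not depend on it.

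**Conclusion.** The point holds as one of lost efficiency and conditional bias. It does not show an error in any stated figure: 12 per facility, 120 and 150 all reproduce without baseline adjustment.

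Against a raw-score analysis, adjustment raises power from 80.4% to between 83.9% and 99.3% over r = 0.3 to 0.77. Against a change score the gain runs from about 18 percentage points (r = 0.3, equal SDs) to under 1 (r = 0.77). If change is the response, the SDs are equal and r is below 0.5, power falls below the planned 80%. Imbalance of at least a third of the target is plausible, at 21% to 35% of trials, but not the expected case. These sizes rest on assumed values of r and of the baseline SD, and on reading 5.1 as the SD of the follow-up score. The direction does not depend on r or on the baseline SD within the ranges examined.

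**What to change.** In section 4.4, before any analysis of outcome data:

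- name the follow-up short FES-I score as the response of the primary model;
- add baseline short FES-I as a covariate, while still accounting for facility;
- report the baseline-adjusted mean difference, with its 95% confidence interval, as the effect measure in place of the unadjusted decrease.

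The cost is one covariate that is already collected and a few changed sentences. No extra visit or participant is needed, and the sample size can stand. An unadjusted comparison can be kept as a supporting analysis.

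### Short FES-I arm means and their 95% CIs are shown only if facilities do not appear to differ; in a facility-randomised trial they should always be reported, with between-facility variation in the CIs

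*Protocol article*

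**What the plan says.** All references are to the protocol article.

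- **Section 4.4, primary model.** The primary efficacy analysis "will be the comparison between intervention and control groups fitting a fixed-effects ANOVA model". On how facility enters that analysis, the section adds: "Model will include group and facility as independent variables, with facility being a nested factor within group".
- **Section 4.4, display rule.** Short FES-I means with 95% CIs "will be provided for each facility, or by groups if no differences between facilities are observed". The section does not say how a difference is judged to be observed, whether facility then leaves the model, or how the group CI is formed.
- **Section 4.4, contrast.** With no condition attached: "The difference in means between the intervention and control groups will be analyzed".
- **Section 4.4, other models.** The falls analysis follows a similar process, with a fixed-effects logistic model and facility again nested in group. The models over time have random intercepts for participants. No random effect for facility is mentioned.
- **Sections 2.7 and 2.8.** Ten facilities are randomised, five per arm. The sample size uses an SD of 5.1, a difference of 3.8 points and "an intraclass correlation coefficient of 0.1, at least 12 participants will be required per center".

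**The concern.** The display rule and the design disagree. Section 2.7 assumes that facilities differ, since an ICC of 0.1 puts a tenth of the outcome variance between them. When facilities are the randomised units, that variance belongs in the uncertainty of every arm-level mean, whatever a check on the collected data shows. The rule instead lets arm-level reporting turn on facility differences not being seen.

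Read literally, neither branch serves the reader. If no difference is seen, arm means are shown, but no model in the article would put between-facility variance into their CIs. If a difference is seen, the sentence calls for ten facility means and no arm means, although the trial compares arms. At stake is how the primary outcome is presented: whether arm means appear at all, and whether their CIs have the stated coverage.

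**Working it through.** **Inputs.** From section 2.7: SD 5.1, ICC 0.1, difference 3.8, alpha 0.05, power 80%, five facilities per arm, 12 analysed per facility (15 recruited). Assumed here: two-sided tests, normal outcomes, equal facility sizes, 'observed' meaning p < 0.05, and an ICC range of 0.02 to 0.2.

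**1. The plan's own figure.** Unadjusted n per arm = 2 × (1.96 + 0.8416)² × 5.1² / 3.8² = 28.28. With m per facility, 5m = 28.28 × [1 + (m − 1) × 0.1] gives m = 11.71, so 12 (normal-approximation power 80.4%). Then 120 / 0.8 = 150. The stated size reproduces and depends on facilities differing.

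**2. Can the check detect that variation?** The F test of facility within group has 8 and 10(m − 1) df. Under random facility effects the F statistic is scaled by 1 + m × ICC / (1 − ICC).
- m = 12, ICC 0.1: scale = 1 + 1.2/0.9 = 2.333. The critical value on 8 and 110 df is 2.024. Power = P(F > 2.024/2.333 = 0.867) = 55%, so the test misses 45% of the time.
- m = 15, ICC 0.1: power 65%, missed 35%.
- Other ICCs, m = 12 (m = 15): 0.02, power 13% (15%); 0.05, 28% (35%); 0.2, 85% (91%).

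**3. Width of an arm-level CI at ICC 0.1, m = 12.**
- SE ignoring clustering: 5.1/√60 = 0.658.
- Design effect: 1 + 11 × 0.1 = 2.1, with √2.1 = 1.45. True SE: 0.658 × 1.45 = 0.954.
- Half-width ignoring clustering: 2.00 × 0.658 = 1.32. With the true SE and t on 8 df: 2.306 × 0.954 = 2.20. Ratio: 2.20/1.32 = 1.67.

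**4. Coverage in closed form, before any check (ICC 0.1, m = 12).**
- Fixed-effects error: expected mean square 0.9 × 26.01 = 23.41, SE = √(23.41/60) = 0.625. Coverage ≈ 2Φ(1.982 × 0.625/0.954) − 1 = 80.5%.
- Facility ignored: expected pooled variance [110 × 23.41 + 8 × (23.41 + 12 × 2.601)]/118 = 25.5, SE = 0.652. Coverage ≈ 2Φ(1.980 × 0.652/0.954) − 1 = 82.4%.

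**5. Does the check change coverage?** Simulation, 100,000 trials per setting. Each cell gives coverage of a nominal 95% CI for an arm mean over all trials, then only in trials where the check was non-significant.

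| m, ICC | Fixed-effects error | Facility ignored | Facility-level, 8 df |
|---|---|---|---|
| 12, 0.02 | 92.1 / 92.3 | 92.3 / 92.3 | 94.9 / 94.2 |
| 12, 0.05 | 87.5 / 87.8 | 88.2 / 88.1 | 95.0 / 93.2 |
| 12, 0.1 | 80.5 / 81.1 | 82.4 / 81.6 | 95.0 / 90.6 |
| 12, 0.2 | 67.6 / 68.2 | 72.0 / 69.1 | 95.0 / 82.9 |
| 15, 0.1 | 77.3 / 78.0 | 79.2 / 78.4 | 95.0 / 89.1 |

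At ICC 0.1 the first two columns move by about one point when the check is applied. The shortfall is there without it, because the error term lacks between-facility variance. The last column shows that a sound interval reaches 95% when always reported, but not when shown only after a non-significant check, since those are the trials in which facilities happened to look alike.

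**The case against.** The strongest reply has four parts.

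1. **The check does not cause the narrow CIs.** A reader might infer that a missed facility difference is what makes the group CIs too narrow. The working does not support that: coverage with facility ignored is 81.6% after a non-significant check and 82.4% with no check. The cause is treating facility as fixed or leaving it out. This part stands, and deleting the condition alone would repair no CI.
2. **The main inference does not depend on the rule.** A reader might infer that detecting facility differences cancels the arm comparison. Section 4.4 says otherwise, because the difference in means is analysed unconditionally. This part stands; the rule governs which means and CIs are shown.
3. **Much is read into one sentence.** The article names no test or threshold, does not claim that facilities are proven equal, and does not say that facility is dropped. This stands too. The 45% figure needs the 5% F test as an assumption. Leaving the criterion undefined adds discretion, however, and the rule is itself stated text rather than detail deferred to another document.
4. **Correcting the primary model would leave only a display preference.** This stands only in part. The sentence would still withhold arm means when facilities differ, and an otherwise sound 8-df interval shown only after a non-significant check would cover 90.6% at ICC 0.1 with 12 per facility.

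Carry-over to falls is uncertain. Section 4.4 speaks of a similar process, but for falls it states a comparison by odds ratios with no facility condition.

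**Conclusion.** The point holds in a limited form: the display rule is wrong for this design and should be changed. It makes arm-level reporting of the primary outcome depend on a check that, if it is a 5% F test, misses the plan's own facility variation 45% of the time with 12 per facility and 35% with 15. Failing to see a difference is therefore no ground for leaving facility out.

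The coverage shortfall is a property of the error term, not of the check: about 80-82% for a nominal 95% CI at the planned ICC with 12 per facility, and about 77-79% with 15. It is modest at ICC 0.02 and severe at 0.2, so its size rests on how far facilities really differ. It also rests on the group CI coming from the stated fixed-effects model or from patients pooled across facilities. The article does not give the formula, but none of its models supplies between-facility variance.

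**What to change.** In section 4.4, delete the condition that allows group-level results only when facilities appear alike, and state instead:

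*Arm means of the short FES-I and the between-arm difference will be reported at every visit with 95% CIs, whatever any comparison between facilities shows. The CIs will include between-facility variation, either from the ten facility means with 8 df or from a model with a random facility effect and a small-sample correction. Facility means will be shown descriptively, with the estimated ICC.*

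Make this change together with any correction of the fixed-effects treatment of facility, since the CIs improve only if the error term changes as well. Apply it to falls only if the display rule is meant to carry over; one clause can settle that.

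The cost is a short rewording, with no new patients or data. The price is wider CIs: about 1.45 times in SE terms at ICC 0.1 with 12 per facility, and about 1.7 times in half-width with 8 df.
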